### Sample size calculation

To demonstrate an effect size of 0.50 (based on a meta-analysis on psychological treatment in mild depression), 66 patients are needed in each group (power 80%, significance level 5%) [49]. Taking into account a dropout of 25%, in total 176 patients will be included. With an annual intake of 450 LC and HNC patients, 30% having psychological distress, and 50% willing to cooperate, and an inclusion period of 2.5 years, feasibility of the study is guaranteed.

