### Study sample

Inclusion criteria are: treatment for UICC stage I-IV lung or head and neck carcinoma: ICD-10 C00-C14 (lip, oral cavity and pharynx), C32 (larynx), C33 (trachea), C34 (lung); psychological distress or possible or probable cases of depression or anxiety as assessed by the Hospital Anxiety and Depression Scale (HADS; HADS-D > 7 or HADS-A > 7 or HADS-total > 14).

Exclusion criteria are: other (neurological) diseases causing cognitive dysfunction; no motivation to undergo psychological therapy; current treatment for a depressive or anxiety disorder; end of treatment for a psychiatric disorder less than two months ago; high suicide risk; psychotic and/or manic signs; too little knowledge of the Dutch language to fill out the questionnaires.

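### The stated recruitment rates give about 169 patients in 2.5 years, 7 short of the 176 required, so the claim of guaranteed feasibility is not supported (minor)

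*Protocol article*

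**What the plan says.** All the relevant figures are in the section Sample size calculation of the protocol article. The target comes first: "To demonstrate an effect size of 0.50 (based on a meta-analysis on psychological treatment in mild depression), 66 patients are needed in each group", at 80% power and a 5% significance level. It is then inflated: "Taking into account a dropout of 25%, in total 176 patients will be included". The same total is given in the Abstract and under Design.

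The feasibility argument follows directly: "With an annual intake of 450 LC and HNC patients", then "30% having psychological distress, and 50% willing to cooperate, and an inclusion period of 2.5 years, feasibility of the study is guaranteed". The product of the four inputs is not shown.

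The section Study sample lists exclusions that apply to patients who are already distressed, among them "current treatment for a depressive or anxiety disorder; end of treatment for a psychiatric disorder less than two months ago". It also excludes cognitive dysfunction, high suicide risk, psychotic or manic signs, too little Dutch, and lack of motivation for psychological therapy. No rate is given for any of these.

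**The concern.** A target, four recruitment inputs and a conclusion stand together in one paragraph, and the conclusion is worded as a certainty. A reader will take it that the inputs multiply to at least 176. They do not, so the paragraph contradicts itself. This is not a detail that a condensed article would leave to a fuller document, because both the inputs and the conclusion are printed.

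What is at stake is whether the planned inclusion period and the planned sample size agree. If they do not, either the period or the expected power has to be restated.

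**Working it through.** **Inputs, all from Sample size calculation:** effect size 0.50; power 80%; significance level 5% (sidedness not stated, two-sided assumed); 66 per group; dropout 25%; total 176; intake 450 per year; 30% distressed; 50% willing; 2.5 years.

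**1. The plan's own sample size.**
- Two-group comparison of means at d = 0.50, two-sided 5%, 80% power: 63 per group by the normal approximation, and 63.8, so 64, by the t-test. The stated 66 is slightly above both and has 81.4% power by the t-test.
- Dropout: (2 x 66) / (1 - 0.25) = 132 / 0.75 = 176. The total reproduces exactly.

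**2. Recruitment yield.**
- Distressed per year: 450 x 0.30 = 135.
- Willing per year: 135 x 0.50 = 67.5.
- Over 2.5 years: 67.5 x 2.5 = 168.75.
- Shortfall: 176 - 168.75 = 7.25 patients; 7.25 / 176 = 4.1%.

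**3. Time needed at the stated rates.**
- 176 / 67.5 = 2.61 years = 31.3 months, about 1.3 months beyond the stated 30.
- The first whole month that suffices is 32: 67.5 / 12 = 5.625 per month, and 5.625 x 32 = 180; at 31 months the yield is 174.4.

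**4. Power if recruitment stopped at 2.5 years.**
- 168 x 0.75 / 2 = 63 evaluable per arm.
- t-test power with 63 per arm at d = 0.50, two-sided 5%: 79.5%.

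**5. What would close the gap, changing one input at a time.**
- Intake: 176 / (0.30 x 0.50 x 2.5) = 469.3, about 470 per year.
- Share distressed: 176 / (450 x 0.50 x 2.5) = 31.3%.
- Share willing: 176 / (450 x 0.30 x 2.5) = 52.1%.

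Each of these only just reaches 176, before any deduction for the exclusion criteria.

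**The case against.** The strongest reply is that the discrepancy is small and the inputs are round planning figures. A distress rate of 31.3% or a willingness rate of 52.1% would remove it, and 66 per group is already above the minimum, so even the short sample has almost 80% power. This stands, and it sets the severity. It does not rescue the sentence, because rounding could make the figures barely sufficient but could not make them a guarantee.

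A second reply is that the pool may be larger than 450 a year. The Design section screens every lung or head and neck cancer patient who attends follow-up at least one month after treatment, with no upper time limit, and also allows screening by telephone. If intake means new patients only, patients treated in earlier years would add to it. That is possible, but the article neither says so nor gives a number. For the same reason, a deduction for patients who never reach a follow-up visit should not be pressed: it looks at only one side of an ambiguous denominator.

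A third reply concerns the exclusions. Lack of motivation may already be contained in the 50% who are willing, and the article does not say whether that 50% is net of the other criteria. This also stands. It can be said that no deduction is shown, but not how large one would be.

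**Conclusion.** The point holds as a minor internal inconsistency. On its own figures the plan yields about 169 patients in the stated period against a requirement of 176, a gap of 7 patients (4%). That means 1.3 more months or, if recruitment stopped at 2.5 years, about 79.5% power. The recruitment result needs no outside assumption; the power figure assumes a two-sided t-test and the stated 25% dropout. The inputs leave no margin for exclusions or for a lower distress rate.

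Three stronger readings are tempting, and the article does not support them:

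- **That the trial will close short and underpowered.** No section sets a calendar stop or ties resources to the 2.5 years, while 176 is given as the number of patients in three places. If that number governs, the effect is a slightly longer recruitment period and no loss of power.
- **That exclusions will cause a large shortfall.** If 10% to 20% of willing patients were excluded, the yield would be 168.75 x 0.90 = 151.9 to 168.75 x 0.80 = 135. Those rates are purely assumed, and part of the loss may already be in the 50%.
- **That 30% is optimistic because the Background gives 20-30%.** That range is for co-morbid anxiety or depression. Eligibility needs only one of three HADS thresholds, so the two quantities need not be the same.

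**What to change.** Show the product in Sample size calculation and make the conclusion agree with it, in one of two ways:

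- keep 176 and give the inclusion period as at least 32 months on the stated rates; or
- keep 2.5 years and state the expected 168 patients, 63 evaluable per arm and about 79.5% power.

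In either case delete the word guaranteed, and say whether the 50% willing is net of the exclusion criteria. If it is not, enter an expected exclusion rate and lengthen the period to match. If patients treated in earlier years are meant to fill the gap, state how many are expected.

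The cost is a few restated figures and either a slightly longer planned period or a power about half a percentage point below 80%. The design, the sample size and the analysis are unaffected.

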## Discussion

There is a rising need towards screening for physical and psychosocial problems and the need for supportive care in routine clinical practice through patient-reported outcomes (PRO’s) [50-54]. The use of PRO’s has proven to facilitate communication concerning quality of life between patients and health care professionals [55-57]. Evidence that this approach may influence patient outcome or improve quality of life is scarce. Luckett and colleagues [54] recommend additional efforts to strengthen the effects of screening, such as using more tumour specific (instead of generic) PRO’s, improving the interpretability of feedback for both medical staff and patients, and training patients in self-efficacy. Organising supportive care according to the chronic care model [58] and providing evidence based supportive care can also improve disease management in cancer patients.

Disease management refers to a system of coordinated comprehensive care along the continuum of the disease across health care delivery systems, with a specific focus on self-management. Other forms of providing supportive care comprise integrated care, transmural care, collaborative care, case management, and stepped care. In oncological settings, recent projects as “Supporting transmural oncological care” [59] and “Integrated care” [60] revealed that supportive care coordination improves supportive care delivery in cancer patients. A review on professional patient navigation in head and neck cancer patients showed that the presence of a professional care navigator leads to higher patient satisfaction, shorter duration of hospitalization, fewer cancer-related problems, better emotional quality of life, and patient empowerment [61].

At present, in VU University Medical Center in Amsterdam, The Netherlands, efficient structured monitoring of quality of life by a touchscreen computer-based data collection system “OncoQuest” is implemented in routine clinical practice [15,62]. Patients can independently fill in the EORTC QLQ-C30, and tumour specific modules, and the Hospital Anxiety and Depression Scale (HADS) on a touchscreen. It takes on average 9 minutes to complete the questionnaires. Data are processed in real-time and care providers can watch the results by clear charts (the well-being profile) on a computer in their consulting rooms and, if indicated, set up a custom-made supportive care plan. Nurses are trained as care navigators to arrange the supportive care according to the disease management principles.

From an economic perspective and in an age of increasing numbers of cancer survivors and increasing shortages of health care personnel, it is relevant to integrate cost-effective health care options including e-health applications into a stepped care approach, as in the presented RCT. This fits right in with the importance that patient organizations, policy makers and researchers currently attach to e-health self-management tools.

Beside assessing overall efficacy of a stepped care approach targeting psychological distress in cancer patients, also insight will be obtained into possible determinants of the need for psychosocial care and success of a stepped care approach. These possible determinants include sociodemographic and disease and treatment related parameters, comorbidity, and quality of life.

Knowledge transfer of the results of the project on efficacy of stepped care targeting psychological distress in cancer patients into the scientific community includes submitting papers to (inter)national peer-reviewed journals, proceedings, and news letters and presenting papers at national and international conferences, both in early pilot stages and after conclusion of the project.

In case of positive results of this RCT on effectiveness, a second step aims at adaptation and maintenance of the stepped care approach to bring the evidence-based practice regarding improving distress in cancer patients into consistent and appropriate use in all oncological centers in the Netherlands. A sharing mechanism will be designed to facilitate adaptation and maintenance such as informing the Dutch Lung Cancer Study Group, Dutch Society of Pulmonologists (NVALT), Netherlands Society of Otorhinolaryngology and Cervico-Facial Surgery, Dutch Head and Neck Oncology Cooperative Group (NWHHT), Dutch Society of Psychosocial Oncology, oncological and psychiatric nursing societies and patient societies, to structure the results of this project into implementation projects in all oncological centers throughout The Netherlands. Guideline committees will be informed and advised to adapt the Nation-wide Guidelines on Laryngeal (2010, version 3.0), Lung (2004, version 1.0), Oral Cavity and Oropharyngeal (2004, version 1.4) and Hypopharyngeal (2010, version 2.0) Cancer [63-66].

The bottom line of the stepped care approach is healthier patients, more satisfied care providers, and cost savings by empowering both professionals and patients.

### Ethical considerations

This study is conducted in accordance with the Declaration of Helsinki and in accordance with local laws and regulations. Eligible patients are fully informed about the study and asked to participate. The patients receive a patient information sheet and have ample opportunity to ask questions and to consider the implications of the study before deciding to participate. Patients consent is noted on an informed consent form compliant with the local and ethical regulations. If during the study the patient for whatever reason no longer wishes to participate, the patient is allowed to withdraw his consent at any time. The study protocol has been approved by the Medical Ethical Committee of VU University Medical Center, Amsterdam, The Netherlands.
